**Synopsis**

Female Genital cutting is now increasingly practiced by medical doctors. This trend of medicalization is a cause of concern and goes against every ethical code of conduct enshrined in the medical fraternity’s world over. At present nothing is known about the practice in Malaysia hence the proposed study to determine the practice and the factors which promote the practice among doctors.

**Abbreviations and acronyms**

FGC – Female Genital Cutting

FGM – Female Genital Mutilation

**Introduction**

The term Female Genital Mutilation/Cutting (FGM/C) refers to all procedures involving partial or total removal of the external female genitalia, or any other injury to the female genital organs for non-medical reasons. There are several types defined by the World Health Organization (WHO) [1] which varies within and between countries

**Type I:** Partial or total removal of the clitoris and/or the prepuce (clitoridectomy). Variation include type Ia - removal of the clitoral hood or prepuce only and type Ib - removal of the clitoris with the prepuce.

**Type II:** Partial or total removal of the clitoris and the labia minora, with or without excision of the labia majora (excision). Variations include, type IIa - removal of the labia minora only, type IIb - partial or total removal of the clitoris and labia minora, type IIc - partial or total removal of the clitoris, labia minora and labia majora.

**Type III:** Narrowing of the vaginal orifice with creation of a covering seal by cutting and apposition the labia minora and/or the labia majora, with or without excision of the clitoris (infibulation). Variations include type IIIa - removal and apposition of the labia minora, type IIIb - removal and apposition of the labia majora.

**Type IV:** Unclassified; all other harmful procedures to the female genitalia for nonmedical purposes, for example, pricking, piercing, incising, scraping and cauterization.

It has been estimated that worldwide more than 200 million girls and women have undergone some form of FGM/C [2], and approximately 3.6 million girls are cut each year. The decline in prevalence, despite decades of campaigning and even criminalizing FGM, is slow [3] probably because of the strong cultural and religious value and believe placed on this [4]. Although most of those who circumcise are traditional healers [5] who usually do not have any medical training and perform without any anaesthesia nor sterilization [6], more parents are choosing to have their daughters undergo the procedure by a health care provider preferably in a clinic to minimize pain and complications [7]. This trend known as medicalization of FGM/C is a serious global concern [8]. Medicalization are procedures performed by health care professionals or the use of medical instruments, antibiotics and/or anaesthetics by traditional practitioners also known as pseudo-medicalization [9]. The WHO defines Medicalization as the “situation in which FGM is practiced by any category of health-care provider, whether in a public or private clinic, at home, or elsewhere” [1]. It is estimated that worldwide, more than 18% of FGC is carried out by healthcare workers which include nurses, trained mid wives and other health care professionals, the rates vary between 1% and 74% between countries [10]. The involvement of health-care providers has been labelled as unprofessional and is a violation of the medical code of ethics and is illegal in some countries. Medicalization creates a false impression that the procedure is good for health or harmless and may create a sense of legitimacy for the practice [11]. There is also a concern that medicalization of the practice may develop into financial interest and could propagate the practice in both medicalized and unmedicalized form [10-12]. Most health-care providers who perform FGM/C are a part of the FGM/C practising community in which they serve and often have the same reasons as those requesting to conduct the procedure. Reasons given for the practice by the health care practitioner who conduct FGC are it is a medical indication, others consider it harmless, some perform the procedure because they support the patients socio cultural beliefs, others consider medicalization as a harm reduction and thus prevent the risks associated with FGC performed by traditional practitioners and by not providing the service the community will revert to traditional practitioners. However, there has been reports of financial gains as the motivation for the procedure [1, 10, 13, 14].

**Objectives**

To determine

the extent of medicalization in Malaysia and

the factors which influence the doctors to practice FGC.

**Methodology**

***Study design***: a mixed method (qualitative and quantitative) study design will be used among Muslim medical practitioners registered as members of major medical associations in Malaysia. ***Tools:*** a self-administered questionnaire will be used. The questionnaire along with a client information sheet will be posted to doctors who could reply using a stamped envelope with the investigators address. The questionnaire will have four sections, baseline information, practice, knowledge and future of FGC. For the qualitative part, in-depth interviews with the doctors who practice FGC will be conducted using a semi structured interview guide. ***Study population:*** Because FGC is only performed by Muslim doctors, the investigators will only enrol doctors from large medical associations in the country who have a big number of Muslim medical doctors as members. The associations will be asked to help distribute the questionnaires to their members. The association will be asked to identify those who are interested to participate in the in-depth interviews. There are no similar studies which have been conducted among medical doctors in Malaysia and there are no official statistics concerning the practice of FGC among doctors in Malaysia. However, the investigators believe a substantial number of doctors among the large population of Muslim doctors practice FGC. A sample size of 384 Muslim doctors will allow the study to determine the prevalence of those practising FGC with a confidence interval of ± 5%. For the qualitative part of the study, it is the intention of the investigators to interview the doctors until the data had reached saturation.

| Year | 2018 | | | | | | | | | | 2019 | | | | |
| --- | --- | --- | --- | --- | --- | --- | --- | --- | --- | --- | --- | --- | --- | --- | --- |
| Projects | mar | apr | may | jun | jul | aug | sep | oct | nov | dec | Jan - July | July - sept | Sept – Nov | Nov | DeC |
| Writing proposal | X | X |  |  |  |  |  |  |  |  |  |  |  |  |  |
| Obtaining an ethical approval |  | X | X |  |  |  |  |  |  |  |  |  |  |  |  |
| Grant application |  |  | X | X | X | X | X |  |  |  |  |  |  |  |  |
| Ground work |  |  |  |  |  |  |  | X | X | X |  |  |  |  |  |
| Data collection |  |  |  |  |  |  |  |  |  |  | X |  |  |  |  |
| Data analysis |  |  |  |  |  |  |  |  |  |  |  | X |  |  |  |
| Write up |  |  |  |  |  |  |  |  |  |  |  |  | X |  |  |
| Submission & Conferences |  |  |  |  |  |  |  |  |  |  |  |  |  | X | X |

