**Data management**

All data related to the study will be kept in a cupboard in the principal investigators office which will be locked with access only available to the principle investigator. Every effort will be made to ensure the confidentiality of the participates.

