**Ethical issues**

This study will be ethically conducted with all the participants required to provide an informed consent. The anonymity of the participants is assured, each participant will be assigned a unique code. A submission for ethical approval will be made to the Ritsumeikan Asia Pacific University Research Ethics Committee and a research grant will requested from the KAKENHI grant from Japan Society for the Promotion of Science.

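### Recruiting interviewees through the medical association may reveal to that body which volunteers practise FGC, in conflict with the anonymity the protocol assures

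*Protocol*

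**What the plan says.** The Methodology section of the protocol describes two parts of the study with different recruitment routes.

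- **Survey.** Questionnaires are "posted to doctors who could reply using a stamped envelope with the investigators address". The association's part is distribution only: "The associations will be asked to help distribute the questionnaires to their members".
- **Interviews.** Eligibility is set as "in-depth interviews with the doctors who practice FGC will be conducted using a semi structured interview guide". Recruitment then goes through the association: "The association will be asked to identify those who are interested to participate in the in-depth interviews".

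Two later sections give assurances. Ethical issues states: "The anonymity of the participants is assured, each participant will be assigned a unique code". Data management says that study data will be kept in a cupboard "locked with access only available to the principle investigator", and that every effort will be made to keep participants' details confidential.

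On the part that doctors and other professionals play in the practice, the Introduction says that it "has been labelled as unprofessional and is a violation of the medical code of ethics and is illegal in some countries". The Synopsis speaks in similar terms.

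**The concern.** In most interview studies, expressing interest says little about the person. Here the only doctors wanted are those who practise FGC, so expressing interest comes close to a statement about one's own practice. If the association collects the names, that statement reaches the doctor's own professional body before the study's protections begin.

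Two things are at stake. The first is the participant's position: a doctor who relies on the anonymity assurance may already have been identified to colleagues or officers of the association. The second is the content of the interviews. Doctors who are uneasy about the practice, or whose reasons are hard to admit, have the most cause to stay away. Those who come forward may then be mainly doctors who are open about the practice or support it, and the second objective, on the factors that influence doctors to practise, would be informed by a narrower range of accounts.

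**Working it through.** No arithmetic decides this point. The check is to follow one interview volunteer through the protocol and see where each protection starts.

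1. **Who is eligible (Methodology).** Doctors who practise FGC. No interview group of non-practising doctors is described.
2. **Who collects the names (Methodology).** The association. The protocol gives no alternative, such as interested doctors contacting the investigators themselves.
3. **What the association can infer.** If it knows the interview criterion, which is hard to avoid when it is asked to recruit for those interviews, a name put forward as interested implies a practising doctor. This step is an inference: the text does not say that the association screens for practice.
4. **Where the code starts (Ethical issues).** The study assigns the code to a participant. That happens after the association has the name, so the code protects the study's records and not what the association already knows.
5. **Where the locked storage starts (Data management).** It restricts access to study data held by the principal investigator. It does not cover information held by the association.
6. **Whether any other section closes the gap.** None does. No section keeps a volunteer's practice status from the association.

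The two parts of the study then compare as follows.

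| | Survey | Interviews |
|---|---|---|
| Does taking part imply practising FGC? | No, all Muslim members approached may answer | Yes, by the eligibility rule |
| Association's role | Helps distribute | Identifies interested doctors |
| Does the doctor's response pass through the association? | No, it goes to the investigators' address | Yes, as the text stands |

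The part in which participation itself is revealing thus has the weaker protection.

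**Effect on the interview material.** The Introduction lists several reasons that providers give: a supposed medical indication, belief that the procedure is harmless, support for patients' sociocultural beliefs, harm reduction and, in some reports, financial gain. These are not equally easy to own up to before one's association. Collecting data to saturation, as Methodology and Statistical analysis plan, does not correct a restricted pool: a group of like-minded volunteers can stop yielding new information while some motives have never been heard.

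**The protocol's one computable figure.** The survey size of 384 for ±5% is reproduced by n = z² × p(1 − p) / d², taking 95% confidence and p = 0.5, neither of which the protocol states: 1.96² × 0.25 / 0.05² = 384.16, or 384 after rounding. The present point neither depends on this figure nor changes it.

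**The case against.** The best defence is that the text asks the association for doctors interested in taking part, not for doctors who practise. The association need not be told the criterion, the investigators could screen the names afterwards, and the association need not learn who is finally interviewed. On this reading anonymity means anonymity of the study records, which is why the sentence ties it to a code. Part of this stands. The disclosure is inferred, and it concerns only members who come forward. But the protocol describes no such screening or shielding, and a body that recruits for interviews with practising doctors will usually know what they are about.

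A second defence is that every interview study relies on volunteers, and that the second objective also draws on the chi-square tests and logistic regression of the questionnaire. That also stands in part. A selection effect in the interviews is plausible, not demonstrated, and a private reply slip would still bring only willing doctors. It would, however, remove one avoidable reason for staying away.

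Third, the Introduction refers to illegality in some countries. It does not say that the practice is illegal in Malaysia or that these associations discipline members for it. That is correct, and the point rests only on the protocol's description of the practice as unprofessional and unethical.

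A reader might also infer that members will deny practising FGC on the questionnaire, so that prevalence is underestimated. The documents do not support this. Replies go directly to the investigators and the association does not receive them. Any figure for the bias would need an assumed prevalence and an assumed denial rate that the protocol does not give, and any denial could as well come from the sensitivity of the topic itself.

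**Conclusion.** The point holds for the interview part of the study. As written, the recruitment route may disclose a volunteer's practice status to his or her own professional body. This conflicts with the anonymity assured under Ethical issues and with the confidentiality described under Data management, and the passages must be reconciled.

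The conclusion rests on one assumption: that the association knows, or can tell, that the interviews are for practising doctors. The professional risk applies to those who volunteer through the association, not to all members who practise. The effect on the interview themes is a reasoned possibility of unknown size.

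Three stronger conclusions that a reader might draw are not supported:

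- The prevalence estimate, the sample size and the regression are not shown to be affected.
- It cannot be said that participants were promised freedom from professional risk. The consent text is not at hand, and Ethical issues says only that consent is required, anonymity is assured and a code is assigned.
- The questionnaire codes need not be dropped, since nothing suggests that a code discloses anything to the association.

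The change is worth making because it protects participants, may widen the range of interviewees and costs very little.

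**What to change.** 1. In Methodology, remove the request that the association identify interested doctors, and limit its role to distributing the packs.
2. Put a separate reply slip for practising doctors who are willing to be interviewed in every pack, with its own stamped envelope to the investigators. As all members receive the same pack, receiving a slip reveals nothing, and the slip travels apart from the questionnaire.
3. In Ethical issues, replace the assurance of anonymity for interviewees with one of confidentiality under a unique code. The investigators necessarily know who the interviewees are, so anonymity in the strict sense cannot be offered to them.

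The cost is one extra slip and envelope per pack and a few sentences of protocol text. The design drawback is that an interview volunteer cannot be linked to his or her questionnaire. No planned analysis in the protocol calls for that link. The sample size, the questionnaire codes and the statistical analysis stay as they are.

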**Data management**

All data related to the study will be kept in a cupboard in the principal investigators office which will be locked with access only available to the principle investigator. Every effort will be made to ensure the confidentiality of the participates.

**Statistical analysis**

Quantitative data will be analysed using SPSS version 18 and presented descriptively in tables and graphs. Prevalence of the practice of FGC will be reported. Chi square test was used to determine the factors which were significantly associated with those who practiced FGC. A binary logistics regression will be performed using independent factors which have a p value of 0.2 in the chi square test. Qualitative data will be collected using a semi structured questionnaire. Data will be collected until saturation of information is achieved. Saturation of data is considered to have achieved when no new information is availed from the respondents. The data will then be transcribed manually, organized, coded and recoded using N vivo. The clustered codes will be elicited as common themes by the investigators

**Ethical issues**

This study will be ethically conducted with all the participants required to provide an informed consent. The anonymity of the participants is assured, each participant will be assigned a unique code. A submission for ethical approval will be made to the Ritsumeikan Asia Pacific University Research Ethics Committee and a research grant will requested from the KAKENHI grant from Japan Society for the Promotion of Science.

